### Exploratory clinical validation aims

Explore differences in running gait outcomes within different clinical (injured vs non-injured) and performance (elite vs novice) groups.Explore relationships between real-world running gait and demographic characteristics (e.g., sex, age) in different clinical and performance groups (e.g., those with a previous injury or different performance level).Investigate the usability of the wearable devices in adult runners.

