#### Laboratory testing

Laboratory testing will be conducted at the biomechanics laboratory Northumbria University, Newcastle upon Tyne, United Kingdom. Within the controlled laboratory environment, we will conduct a concurrent data collection with the multimodal, commercial, and research-grade wearables to determine their validation and reliability for running gait analysis compared to laboratory reference standards (3D motion capture and force plates). Recruitment for the laboratory testing began in September 2021 with an expected end date September 2023.

*Participants*. Within the laboratory testing 40 individuals will be recruited, specifically 20 with and 20 without a history of previous lower limb injury (but fully recovered at time of assessment and able to run safely, in line with inclusion / exclusion criteria).

*Laboratory reference set-up*. As previously described, a 3D motion capture and force plate system will be used as the ‘gold-standard’ reference measures.

*Running procedures*. All participants will run overground and, on a treadmill, (Spirit fitness XT485). Participants will be provided with a standardised, neutral cushioning running shoe (Saucony Guide Runner) to wear during testing in order to remove bias [34]. Prior to testing, participants will run on the treadmill at a comfortable speed for a warm-up and to familiarise themselves with running on a treadmill. Participants will be allowed breaks at any point or permitted to abort the trial at any time. For the overground segment, participants will run at a comfortable self-selected speed overground for 10m intermittently, where they will be asked to foot-strike two staggered force plates in the middle of the run (~5m point). Practice trials will be performed prior to data collection to allow participants to adjust their start position to strike the force plates correctly. A total of five successful recordings for each of the left and right leg will be captured. For the treadmill segment, participants will be asked to run at five speeds, four of these speeds will be standardised (i.e., 8, 10, 12 and 14 km/hr) and one speed will be their self-selected speed. Self-selected speed will be determined by the participant’s 5km personal best. The order of speed will be consistent across participants, starting at the slowest speed and progressing to the fastest to ensure the safety of participants. Data will be collected for 60s at each speed.

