#### Real-World environment testing

Data from the novel multimodal, commercial, and research-grade wearables will be collected within real-world environments to test the clinical / performance validity of the wearables (i.e., can they differentiate or provide meaningful data on relevant populations). Recruitment for the real-world environment testing began in June 2023 with an expected end date October 2023.

*Participants*. Within the real-world environment testing 40 individuals, specifically novice/amateur (n = 20) and expert/sub-elite (n = 20) running performance level. Performance level will be based on their 5km running time (i.e., age graded performance % [35]).

*Wearable location*. Each participant will be equipped with the DANU Sports System (socks on both feet), two Axivity AX6 sensors attached to the shoelaces and two DorsaVi ViMove2 sensors on the tibia.

*Running procedures*. All participants, regardless of performance level, will be asked to complete a 5km run on a standardised route in North-East England. The course will be run on a mixture of trail paths and concrete paths, with 174ft elevation gain throughout. Information about conditions (e.g., environment and shoes) and objective load data (e.g., time and pace) will be collected. Participants will wear their own running shoes.

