### Outcome measures

The primary outcome measures for this study are running gait outcomes as measured by the wearables and are described in Table 2. A secondary outcome measures is usability. Usability refers to the effectiveness, efficiency, and user satisfaction rating of a product (various grades of wearables) in an particular environment by a user for a specific purpose (running gait analysis) [40].

**Table 2 pone.0291289.t002:** The primary outcomes measured by each grade of wearable.

Outcome	Definition	Axivity AX6	DorsaVi ViMove2	DANU Sports System	Reference Measure

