To examine the analytical (concurrent) validation of running gait outcomes measured in real-world settings from the various grades of wearables in all real-world testing participants (n = 40), we will compare outcomes across the wearable devices (research, commercial and novel multi-modal) through widely used measures of agreement. The absolute difference, r, ICC, the level of agreement through the Bland Altman plots, 95% LoA, RMSEs will be calculated to evaluate agreement between outcomes generated by each wearable [48].

*Exploratory clinical validation analysis*. To provide an initial exploration of clinical (performance) validation, we will investigate group difference and relationships with clinically (or performance) relevant measures. For group differences (e.g., previous injury history or performance level), analysis of co-variance (ANCOVA), will be conducted to assess for differences between groups (injured vs non-injured, or elite vs novice) in the individual running gait outcomes (e.g., ground contact time etc.) from the novel multimodal, commercial and research-grade wearable devices during the running tasks, while controlling for demographics that are significantly related to the running gait outcomes. Relationships between running gait outcomes and demographic variables (e.g., sex, age, height, weight etc.) within groups (injured vs non-injured, or elite vs novice) will be completed through Pearson correlations within each grade of wearable device (research, commercial, multimodal).

To examine the usability of the wearable devices the SUS scores for each wearable will be calculated and visualised. To investigate differences in participant perception of the usability for each grade of wearable, separate analysis of variance (ANOVA) tests will be performed. The ANOVAs will determine the differences between the SUS scores within the different device grades between participant groups (e.g., injury history, performance level). The relationships between the SUS scores, demographics (e.g., sex, age, age-grade performance), and wearables characteristics (e.g., price, weight, and battery life) will be explored using Pearson correlations [39]. The strength of the correlation will be assessed based on Cohen’s criteria: correlations < 0.30 are considered small, correlations between 0.30 and 0.50 will be considered medium, and correlations > 0.50 are considered strong [53].

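### The laboratory injury-history comparison is planned on wearable outcomes only; repeating it on the reference values from the same runs would let it be read as a result about the devices

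*Protocol article*

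**What the plan says.** The exploratory aims are to "Explore differences in running gait outcomes within different clinical (injured vs non-injured) and performance (elite vs novice) groups". Under Statistical analysis, the exploratory clinical validation paragraph uses ANCOVA to compare the groups, by injury history or by performance level, "in the individual running gait outcomes (e.g., ground contact time etc.) from the novel multimodal, commercial and research-grade wearable devices during the running tasks". The Outcome measures section is consistent with this: "The primary outcome measures for this study are running gait outcomes as measured by the wearables".

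The injury groups belong to the laboratory arm, which recruits "20 with and 20 without a history of previous lower limb injury (but fully recovered at time of assessment" and able to run safely). For that arm, "a 3D motion capture and force plate system will be used as the" gold standard. The initial data processing paragraph has all systems recording at the same time. Table 2 lists a reference measure for each of its eight outcomes. The Data processing section puts all available outcomes in one master table with a column for injury history.

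The only stated use of the reference data is in the analytical validation paragraph: difference, correlation, ICC, limits of agreement and RMSE, in all 40 laboratory participants together. The protocol does not plan the injury contrast on reference outcomes, or agreement by injury group.

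**The concern.** Comparing known groups tests a device only to the extent that one knows whether the groups differ in the quantity measured. Here that is open. The previously injured runners must have recovered, and the injury definition under Data collection is broad: a restriction of running for 7 days, or one consultation with a health professional, is enough. The true gait difference may be small or absent.

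If a wearable shows no group difference, the planned contrast alone cannot separate an insensitive device from groups that do not differ. If it shows one, the contrast alone cannot separate a real gait difference from device error that depends on group. The data that would help are already recorded in the same runs. What is at stake is how an exploratory result is interpreted, and what later studies build on it.

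**Working it through.** **The plan's own figure.** The Sample size calculation section calls 20 per group adequate for the clinical group analysis by a pilot-study rule of thumb. It gives no effect size, SD or power, so the figure can be neither reproduced nor refuted. Every effect size, reliability and bias below is an assumption.

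**Inputs.** n = 20 per group (Laboratory testing); significance level 0.05 (Statistical analysis), taken as two-sided. A two-group t-test stands in for the ANCOVA. The true between-runner SD is set to 1 and the reference is treated as error-free. Reliability ρ is true variance divided by wearable variance; 0.9, 0.75 and 0.5 are borrowed from the cut-points of the protocol's ICC scale.

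**Step 1: power of the contrast.** The noncentral t has 2 × 20 − 2 = 38 degrees of freedom and noncentrality d × √(n/2) = d × √10 = 3.162d. On a wearable the standardised difference shrinks to d × √ρ.

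| True difference | No device error | ρ = 0.9 | ρ = 0.75 | ρ = 0.5 |
|---|---|---|---|---|
| 0.5 SD | 34% | 31% | 27% | 19% |
| 0.8 SD | 69% | 65% | 57% | 41% |

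Without device error, 80% power needs a true difference of 0.91 SD. A null result is thus expected about 66% of the time at 0.5 SD even with a perfect device, and 95% of the time if the groups do not differ.

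**Step 2: what the reference adds.** Simulation with 20,000 runs, 20 per group, random device error SD = √((1 − ρ)/ρ), and an optional device bias present in one group only. Entries are the percentage of runs significant at 5%, for ρ = 0.9 (error SD 0.333).

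| Scenario | Wearable contrast | Reference contrast | Wearable minus reference, by group |
|---|---|---|---|
| No difference, no bias | 5 | 5 | 5 |
| True difference 0.8 SD, no bias | 65 | 70 | 5 |
| No difference, bias 0.8 SD | 65 | 5 | 100 |
| True difference 0.8 SD, bias −0.8 SD | 5 | 70 | 100 |

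The second and third rows look alike on the wearable and differ in both added columns. In the same order, those two rows are 57/70/5 and 57/5/99 at ρ = 0.75, and 41/69/5 and 41/5/69 at ρ = 0.5.

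**Step 3: what pooled agreement already constrains.** With equal groups, a between-group bias b adds b²/4 to the variance of the wearable-minus-reference differences. If the pooled SD of those differences were 0.333 (the ρ = 0.9 case) and all of it were group bias, b could reach 2 × 0.333 = 0.67 SD; for ρ = 0.75 it could reach 2 × 0.577 = 1.15 SD. Pooled agreement therefore caps a differential bias but does not exclude one, and it does not estimate the group difference in reference-measured gait.

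**Step 4: precision of the added quantities.** The 95% half-width is t(0.975; 38) × SD × √(2/20) = 2.024 × SD × 0.316.
- Reference group difference (SD 1): 0.64 SD.
- Group difference in wearable minus reference: 0.21 SD at ρ = 0.9, 0.37 at 0.75 and 0.64 at 0.5.

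For a device that agrees well, the paired difference is about three times as precise as the reference contrast (0.64/0.21). It is the more informative addition.

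**The case against.** The case against is substantial, and much of it stands.

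- **The device question has its own earlier step.** The protocol sets analytical validity before clinical validity and plans agreement and retest statistics in the same 40 runners. A device that agrees poorly would be seen there. A reader might infer that the injury result says nothing about the device, or cannot be attributed at all. The documents do not support that. What is missing is agreement by group and an estimate of the reference group difference.
- **The framing wording belongs to the other arm.** The question "can they differentiate or provide meaningful data on relevant populations" is posed under Real-World environment testing, where the groups are performance levels and no reference system is described. For injury history the plan promises only an initial exploration. A reader might infer that device grades will be ranked on the injury contrast, but no section plans this.
- **The group label is mostly clear.** The abstract says previously injured and never injured, the recruitment text states recovery, and the analysis paragraph mentions previous injury history before its shorthand. Full recovery is required only of the 20 with a history. A reader might infer that currently injured runners are to be compared; the recruitment text rules that out.
- **Sample size is the main limit, and the fix does not change it.** At 0.5 SD, a null on the reference favours no difference over a true difference by only 0.95/0.66 = 1.4, against 0.95/0.81 = 1.2 for a wearable with ρ = 0.5. Positive wearable results do carry information: at 0.8 SD and ρ = 0.5 they are about eight times as likely as under no difference (41% against 5%).
- **Group-dependent device error is hypothetical.** The documents give neither a reason for it nor a size.
- **The reference has error too.** Force plates serve only the overground runs; treadmill timing rests on filtered marker data and visual event identification. The simulated gain is an upper bound.
- **Could this be left to an analysis plan?** Only in part. The protocol itself names the source of the tested outcomes and names only the wearables, although nothing prevents adding the reference.

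**Conclusion.** The point holds as a cheap improvement to an exploratory analysis in the laboratory arm. The injury-history contrast is specified on wearable outcomes only and the reference data are used only for pooled agreement, so the contrast alone shows neither whether the groups differ in reference-measured gait nor whether device error differs by group. It does not invalidate the agreement or reliability results.

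The size depends on assumed effects. Power is about 34% at 0.5 SD and 69% at 0.8 SD before any device error. A true 0.8 SD difference and an equal differential bias are indistinguishable on the wearable (65% each at ρ = 0.9), but separable once the reference is added. These figures rest on an error-free reference, no covariates, and biases chosen for illustration.

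**What to change.** In the exploratory clinical validation analysis, for the laboratory arm only:

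1. Fit the same injury-history ANCOVA to the Table 2 reference value of each outcome.
2. Report the wearable and reference group differences side by side, and the wearable-minus-reference difference by group, all with confidence intervals.
3. Interpret a device's injury-group result relative to the reference contrast, stating that the reference has its own error and that 20 per group leaves both contrasts imprecise.
4. In the exploratory aims and the analysis paragraph, name the groups as previously injured and recovered against never injured, in line with the abstract and the recruitment text.

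The cost is one extra model per outcome (eight outcomes in Table 2) for each running task analysed, plus the group comparison of paired differences, all on data already being collected. No participants or procedures are added. The clinical claim becomes slightly narrower. The real-world performance-level contrast has no reference system and is not covered.

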### Statistical analysis

#### Analysis common to all studies

The statistical analysis will be performed using statistical software SPSS 25 (SPSS Inc., Chicago, Illinois, USA). Demographic characteristics will be summarised using descriptive statistics, including mean, standard deviation, median, minimum, maximum, and inter-quartile range for continuous or ordinal data and percentages for categorical data. The descriptive statistics will be tabulated and presented graphically for clarity. All data will be checked for normality distributed with Shapiro-Wilks tests before conducting parametric tests. Non-normal continuous distributions will be transformed where appropriate to meet the requirements of parametric tests; otherwise, the equivalent non-parametric tests will be adopted. Data will also be assessed graphically (such as histograms or scatter plots) for clarity of information. Statistical significance will be determined at p < 0.05 unless otherwise stated. Due to the experimental nature and novelty of the work and wearable systems, we will not control for multiple comparisons in order to avoid a Type II error.

*Analytical validation analysis*. To examine analytical (concurrent) validation of the wearable devices (research-grade, commercial, novel multimodal) for running gait measurement, we will compare outcomes to relevant reference measures (i.e., force plates for ground contact time) in all laboratory testing participants (n = 40). To compare running gait outcomes from the wearables and reference systems, the absolute difference, Pearson’s correlation (r), intraclass correlations (ICC), the level of agreement through the Bland Altman plots, and 95% Limits of agreement (LoA) will be calculated [48]. Accuracy will be evaluated in terms of root mean squared errors (RMSEs).

To determine test re-test reliability of the wearables, r, and ICCs between the two testing time-points will be calculated [49]. A predefined ICC performance scale will be used, defined as poor (<0.50), moderate (0.50–0.75), good (0.75–0.90) or excellent (>0.90) [50]. ICC is a common statistic for evaluating repeatability and is needed to calculate the minimally detectable change (MDC) [51, 52]. The standard error of measurement (SEM) and standard deviation (SD) will also be calculated. Laboratory based analytical validity and reliability outcomes will be descriptively reported and discussed across research-grade, commercial and novel multi-modal wearable devices.

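### The group ANCOVA screens demographics for significance and leaves out running pace, so an elite-versus-novice difference in speed-linked outcomes cannot be read as a gait difference beyond pace

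*Protocol article*

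**What the plan says.** Under Exploratory clinical validation analysis, the protocol article compares injured with non-injured and elite with novice runners. It uses one ANCOVA per gait outcome from the wearables, "while controlling for demographics that are significantly related to the running gait outcomes". The general threshold is given as "Statistical significance will be determined at p < 0.05 unless otherwise stated", and the plan adds that "we will not control for multiple comparisons in order to avoid a Type II error".

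The only guide to what counts as a demographic is by example. The correlation analysis that follows covers "Relationships between running gait outcomes and demographic variables (e.g., sex, age, height, weight etc.) within groups", and the usability paragraph speaks of "demographics (e.g., sex, age, age-grade performance". Running speed or pace is not named as an ANCOVA covariate.

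Under Real-World environment testing, "Performance level will be based on their 5km running time", with age grading. Both groups of 20 run the same 5 km route, with no speed set. The same section says that "objective load data (e.g., time and pace) will be collected", but the statistical section gives these data no use. Under Laboratory testing, participants run on the treadmill at four fixed speeds (8, 10, 12 and 14 km/h) and at one self-selected speed, and overground at a self-selected speed.

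**The concern.** The field arm asks whether the wearables can tell relevant populations apart or say something meaningful about them. The groups are formed on how fast people run and are then measured while each runner goes at their own pace. By the definitions in Table 2, speed is step length times step frequency, and step time is contact time plus flight time. A faster group must therefore differ in step length, step frequency or both, whatever its gait would be at a matched speed. Tibial acceleration can be expected to follow speed as well. A positive contrast then shows that the device registers pace, which the study already records. It does not show that elite and novice runners move differently once pace is accounted for.

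The screening rule has a second weakness. It chooses covariates from the same data by significance, outcome by outcome, so the adjustment is not known in advance. With an open list of demographics, age-grade performance could enter and adjust the performance contrast for its own grouping variable.

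**Working it through.** **No figure to reproduce.** The Sample size calculation section justifies 20 per group by rule of thumb, with no effect size, SD or power.

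**Inputs.** From the documents: 20 versus 20 and a 0.05 level, taken as two-sided. Assumed, because the documents are silent: a group speed gap of k within-group SDs, a within-group correlation r (in absolute value) between speed and the outcome, a linear relation, and no selected demographic that stands in for speed. Demographics correlated with pace, if selected, would remove part of the effect.

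**Step 1: effect produced by speed alone.** Scale the outcome to a within-group SD of 1 and let it depend on speed only, with no group effect at equal speed. The unadjusted standardised difference is d = r × k. The chance of significance is the two-sample t-test power with 38 degrees of freedom and noncentrality d × √(20/2).

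| Speed gap k | r = 0.3 | r = 0.5 | r = 0.7 |
|---|---|---|---|
| 1 SD | d = 0.30: 15% | d = 0.50: 34% | d = 0.70: 58% |
| 1.5 SD | d = 0.45: 28% | d = 0.75: 64% | d = 1.05: 90% |
| 2 SD | d = 0.60: 46% | d = 1.00: 87% | d = 1.40: 99% |

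Simulation of the same model (3,000 runs per cell) agrees: 16/34/57% at 1 SD, 29/64/89% at 1.5 SD and 45/87/99% at 2 SD. If the outcome is unrelated to speed, the figure stays at about 5%.

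**Step 2: with speed as a covariate.** In the same simulations, the group contrast is significant in 4.2% to 5.4% of runs in every scenario.

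**Step 3: cost in precision.** The ratio of adjusted to unadjusted standard error is approximately √[(1 − r²)(1 + k²/4)].
- k = 2: √(0.91 × 2) = 1.35 at r = 0.3 and √(0.51 × 2) = 1.01 at r = 0.7 (simulated: 1.39 and 1.05).
- k = 3: √(0.91 × 3.25) = 1.72 at r = 0.3 and √(0.51 × 3.25) = 1.29 at r = 0.7 (simulated: 1.78 and 1.35).

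**Step 4: does screening make devices disagree?** Simulate two devices measuring the same outcome, with 40 runners, four covariates each correlated 0.3 with the outcome and unrelated to group, and device reliability 0.80 to 0.95 (3,000 runs per setting).
- The selected covariate sets differ in about 36% to 60% of runs when there is no group effect.
- With no group effect, the two devices disagree on group significance in 3.6% to 6.2% of runs with screening and 3.4% to 6.1% with all four covariates fixed.
- With a group effect of 0.8, they disagree in 12% to 23% with screening and 10% to 21% with the fixed set.

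Screening adds at most about 3 percentage points. Most of the disagreement is measurement error, which a fixed set does not remove.

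**The case against.** The strongest reply is that pace is not an ordinary confounder here, because it is part of how the groups are defined. Whether a device separates known groups running at their own pace is a fair question, and the unadjusted contrast answers it. Adjusting for pace asks a different question, and does so with a near-copy of the grouping variable in the model. This stands. A reader might infer that the unadjusted contrast is invalid or that only the adjusted one may be reported, and the documents do not support either.

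Four other stronger readings are tempting.

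- **The contrast mostly re-measures pace.** The documents give no pace gap, slope or SD. Age grading loosens the link between group and raw pace, and the concern is weaker for foot-strike pattern and symmetry.
- **A false positive is near certain.** That needs assumed raw-unit inputs. For example, a gap of 1.0 m/s, contact time falling 30 ms per m/s and an SD of 20 ms at fixed speed give d = 1.5 and 0.996. Allowing an assumed within-group speed SD of 0.3 to 0.7 m/s lowers this to 0.99 to 0.89.
- **The adjustment necessarily differs by device.** The text does not say that the screen runs separately per device. The phrase "will be completed through Pearson correlations within each grade of wearable device (research, commercial, multimodal" belongs to a separate within-group correlation analysis. The covariate sets can differ, but Step 4 shows little effect on group significance.
- **The injury contrast is equally exposed.** The four fixed treadmill speeds protect it. Only overground and self-selected treadmill running are open to the concern.

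It is also true that the analysis is labelled exploratory, that the sample-size section leaves control of relevant variables to future research, and that the agreement and reliability analyses do not use this rule. This lowers the severity. It does not make a contrast interpretable as gait beyond pace when a recorded variable can explain it.

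**Conclusion.** The concern holds in a limited form. The covariate rule is stated in the text, so it is a choice fixed badly and not a detail left for later. As written, a significant elite-versus-novice difference in speed-linked outcomes cannot be read as more than a difference at each group's own pace. Under speed gaps of 1 to 2 within-group SDs and correlations of 0.3 to 0.7, pace alone yields significance in about 15% to 99% of trials, against about 5% with speed in the model. The width of that range reflects inputs that the documents do not give. Data-driven screening is a lesser fault: it leaves the adjustment unpredictable but hardly changes which devices detect a group difference, provided that covariates are unrelated to group. Severity: should be fixed. No primary validity or reliability result depends on it.

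**What to change.** - Replace the significance screen with one prespecified covariate set for every outcome and device, for example age, sex and height. State that age-grade performance is not a covariate.
- Report the performance contrast twice: without pace, labelled a difference at own pace, and with mean 5 km pace as a covariate, labelled a difference at equal pace. Base any statement about gait beyond speed on the second.
- Make the fixed treadmill speeds the main injured-versus-non-injured comparison, and add measured speed as a covariate for overground and self-selected treadmill running.
- Do not move the performance comparison to the laboratory arm. It was recruited 20/20 on injury history, so performance-group sizes there are unknown and may be entangled with injury.

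The cost is a wording change. Field pace is already collected, and the laboratory analysis needs the actual running speed to be kept. The drawback is precision: the pace-adjusted standard error is about 1.05 to 1.4 times the unadjusted one at a 2-SD speed gap and 1.3 to 1.8 times at 3 SD. With so little overlap the estimate also leans on the assumed linear relation. The report should show the overlap in pace and say when the adjusted estimate is too imprecise to interpret.
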